## I. Format of the paper

- There will be four sets of analyses reported in the paper and appendix:
  - Primary analyses run on the full sample, identified ex-ante in this document
  - Secondary analyses are additional hypotheses (i.e., not fundamental) of the data identified ex-ante in this document
  - Ex-post analyses are exploratory analyses that we will determine ex-post, after data analysis
  - Robustness checks are additional tests to check the robustness of results to assumptions made in the main analyses
- In the main body of the paper, we will report all primary analyses identified ex-ante
- We will also have an “additional analyses” section in the paper or supplementary materials which will report select findings from secondary and ex-post analyses (identified as such)
- All secondary and ex-post analyses not reported in the additional analyses section of the main paper will be reported in the supplementary materials
- All primary and secondary analyses will be recorded in the Open Science Framework prior to conducting any analyses

## II. Transformed variables

- All variables (with the exception of the binary indicator for male gender) are transformed to have mean zero, variance one, and a normal-distribution shape by:
  1. Calculating a percentile rank of the underlying variable
  2. Applying the inverse normal function to the percentile rank

## III. Primary analyses

- We will test, in separate regressions, the relationship between each of 11 primary outcomes and 2 primary measures of self-regulatory and delay ability for a total of 22 primary analyses
- We will control for gender in all analyses (note that we do not control for age at the time of the delay task because, in the delay time analyses where age would be relevant, the variable we use—deviation from expected delay time—already takes age into account)
- Each regression will be of the following form

$$y = \alpha + \beta_1 \times x + \beta_2 \times male$$

where  $y$  is one of the primary outcomes,  $x$  is one of the primary right hand side variables (deviation from predicted delay time or self-regulatory competence),  $male$  is a dummy for being male, and  $\alpha$  is a constant.  $\beta_1$  is the coefficient of interest

- In analyses with savings rate as the primary outcome measure, we will also include permanent income as an additional covariate

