## VII. Ex-ante hypotheses and notes on analysis

- We hypothesize that behavior in the marshmallow delay task will not have much explanatory power on mid-life outcomes. Performance on the task is a noisy measure of self-control and the effect is diluted as subjects' life trajectories have likely changed in the 30-40 years since the marshmallow task. We hypothesize that we will not find statistically significant results in our primary analyses predicting mid-life outcomes from behavior in the marshmallow delay task
- We hypothesize that correlations with indices of self-control behavior over the first 40 years of life will have more predictive power than performance on the marshmallow task alone. These correlations are likely to be higher because: (1) self-control is measured as recently as late 30s, much closer to the mid-life outcomes than the marshmallow task, (2) these measures have been successful in earlier work predicting life outcomes, and (3) index scores tend to be more successful than single measures of individual differences since they average out more noise
- We expect that the self-regulatory competence index will have low correlation with the outcome variables
- In this wave of data collection, we have responses from 113 of the original 550 Bing participants. We recognize that attrition and media attention to previous results from this sample are important issues; however, we make no assumptions of how these issues may impact results
- The focus of this paper is limited to the relationships and variables outlined in this document. Future analyses may test hypotheses using additional variables from the same wave of data collection. The analyses we plan to do in this project will be restricted to predictions of the outcomes measured using the survey this team conducted. The approach to handling multiple testing problems outlined in this analysis plan is designed specifically for this set of analyses will not affect future analyses addressing different questions, using variables based on other waves, past and future, of data collection from the Bing sample

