#### **D. Self-regulatory competence: index of behavior to 2003**

- We will create a measure of self-regulatory competence as an index of behavior that includes the expected deviation from predicted delay time (in uncensored log seconds) and self-control indices in 1984, 1993, and 2003. The index will be an average of each of the four measures (transformed by the inverse normal transformation), giving equal weight to each measure. The final index will be re-transformed using the inverse normal percentile transformation to obtain a measure of persistent self-regulatory competence
  - Expected deviation from predicted delay time in uncensored log seconds
  - Self-control index in 1984
  - Self-control index in 1993
  - Self-control index in 2003
- This aggregate measure will only be calculated for subjects with at least one self-control score

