#### **E. Age in months at time of original delay experiment**

- Subject’s age in months when first completed the marshmallow delay experiment

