## H. Permanent Income

- Permanent income is defined as the average of household income in the last calendar year and at age 35 divided by the number of adults living in the household:

$$\frac{\text{Average of household income in the last calendar year and at age 35 (scaled for inflation)}}{\text{Number of adults in the household}}$$

- We use the average of household income in the last calendar year and at age 35 (scaled for inflation) if both are available and non-zero. If either measure is missing or zero, we use only the available, non-zero income
  - Household income in last calendar year is the sum of household income from the following sources:
    - *In the last calendar year, what was your pre-tax household income from the following sources? Income from wages or salaries, Income from self-employment, Income from public and private pensions, Income from Social Security, Income from unemployment benefits, Income from any other social benefits, assistance, or grants (e.g., veteran's benefits, disability benefits), Income from investments, savings, insurance, or property (including dividends, interest, and rent from rental property), Income from any other sources*
- Stated total household income at 35 is scaled for inflation to the last calendar year using the CPI when the respondent was 35 and the CPI in the year prior to when the respondent completed the survey
  - *What was the total pre-tax annual income of your household when you were 35 years old? (If you don't know the exact figure, please give your best estimate.)*
- Number of adults currently living in the household
  - *Including yourself, how many people in each of the following age groups is currently living in your household? Adults*
  - Note: if this question was left blank, we assume two adults if married and one adult if never married or divorced

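### The stated reason for leaving age out of the primary models covers the delay regressions but not the 11 regressions on the self-regulatory competence index

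*SAP*

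**What the plan says.** Section III of the SAP plans 11 outcomes by "2 primary measures of self-regulatory and delay ability for a total of 22 primary analyses". Each model contains the key variable and a male indicator. The one addition is for a single outcome: "In analyses with savings rate as the primary outcome measure, we will also include permanent income as an additional covariate".

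The omission of age at the task is explained in a parenthesis. The reason given there is confined to some of the models, "in the delay time analyses where age would be relevant", whose key variable already allows for it. Section X.A bears this out: the Tobit random effects model has a linear term for age in months at the task.

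For the second key variable, Section VIII.D says "The index will be an average of each of the four measures", equally weighted: the delay deviation and the self-control indices for 1984, 1993 and 2003. Section VIII.C standardises the questionnaire responses within rater (1984) or within participant (1993 and 2003), then applies inverse-normal transformations and imputes missing subscales. It describes no age adjustment.

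The only age variable defined is in Section VIII.E: "Subject’s age in months when first completed the marshmallow delay experiment". Age at survey is not in the secondary models (IV.B), the diagnostic-condition models (IV.C), the robustness checks (V) or the multiple-imputation model (X.E).

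**The concern.** The parenthesis treats age as a matter for the delay analyses alone. In the index regressions, only a quarter of the key variable has been adjusted for age; the rest are ratings taken in fixed calendar years. If respondents differ in age, they were rated at different ages and their outcomes were measured at different ages. Should age be related both to the rated self-control and to an outcome, the index coefficient would carry part of the age association.

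The outcomes most open to this are those that build up over time: net worth, net worth over permanent income, and the last-year part of permanent income. The other part, income at age 35, is already aligned to a common age.

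The planned safeguards address other problems. False discovery rate control deals with multiplicity. The empirical Wald test resamples the key variable, which breaks any link with age in the reference distribution, so it cannot reveal or correct age confounding. Under Section I, an age adjustment introduced after analysis would have to be labelled ex-post.

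**Working it through.** **Count.** 11 outcomes × 2 key variables = 22, as Section III states. Of these, 11 use the index.

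**Weights.** Four equal parts: 1/4 delay deviation (adjusted for age at task) and 3/4 self-control indices (no age adjustment described).

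**Inputs for size.** The outcome list in Section III.A gives n = 109 for net worth. Section VI.C gives a prior mean correlation of 0.15 for the index. The correlations of age with the index and with an outcome are not in the document. I assume 0.1-0.3 and 0.1-0.2 respectively.

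**Formulas.** If the index has no true effect and age is omitted, the spurious standardised coefficient is b = r(index, age) × r(outcome, age), taking gender as unrelated to age. Its standard error is SE = √[(1 − b²)/(n − 3)]. The rejection rate at nominal two-sided 5% is 1 − Φ(1.96 − b/SE) + Φ(−1.96 − b/SE).

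**Results at n = 109** (SE ≈ 1/√106 = 0.097):

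| r(index, age) | r(outcome, age) | b | b / 0.15 | Rejection rate |
|---|---|---|---|---|
| 0.1 | 0.1 | 0.01 | 7% | 5.1% |
| 0.1 | 0.2 | 0.02 | 13% | 5.5% |
| 0.2 | 0.2 | 0.04 | 27% | 7.0% |
| 0.3 | 0.2 | 0.06 | 40% | 9.5% |

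The index exists only for the 110 of 113 subjects with at least one self-control score (Section X.E), so the net worth regression may have as few as 109 − 3 = 106 subjects. The SE would then be 1/√103 = 0.099, which changes nothing of substance.

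**Cost.** At n = 109, with intercept, key variable and gender, the residual degrees of freedom fall from 106 to 105.

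**Precision in the delay regressions.** If age explains r² = 0.01 of the outcome variance, the residual mean square changes by a factor of 0.99 × 106/105 = 0.999, which is no gain. At r² = 0.04 the factor is 0.96 × 106/105 = 0.969, so the SE falls by about 1.6% (√0.969 = 0.984).

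**Availability of age.** Section VIII.H rescales earlier income "using the CPI when the respondent was 35", which requires knowing the year each respondent reached that age. Section IX reports that age was examined when outlying net worth, assets and debts were checked.

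**The case against.** The strongest reply is that Section III misstates nothing. Its reason concerns age at the task in the delay analyses, and there it is correct; it is not offered as a reason for omitting current age. That stands. The gap is that no reason at all is given for the index regressions.

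Four stronger readings are tempting, and the document does not support them.

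- A reader might take the three self-control parts to be raw ratings that rise with maturity. They are standardised within rater or participant, which removes a general upward shift and leaves only relative shifts between items. For small age differences among adults in 1993 and 2003, a strong age gradient is not obvious.
- A reader might infer a wide spread of birth years from the remark that life trajectories "have likely changed in the 30-40 years since the marshmallow task". That interval cannot be read literally as a range. Section VIII.Q puts subjects at about 18 in 1984, hence about 46 at the 2012 survey. A task 30 years before 2012 would fall in 1982, when such a subject was about 16, not of preschool age. Some spread is likely, but no range or standard deviation is given.
- A reader might call age a common cause in all 11 index regressions. Accumulation is a plausible mechanism for the wealth outcomes and last-year income. None is evident for educational attainment, the money-sooner-or-later choices, credit card misuse, forward-looking behaviors or social status.
- A reader might want age in all 22 models for precision. The calculation above shows that the gain in the delay regressions is negligible.

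It may also be said that Section VII frames the aim as prediction, for which few covariates suffice. That has some force. But the plan removes age from the delay measure and adjusts every model for gender, so it does not want demographic differences credited to self-control.

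**Conclusion.** The point holds in limited form. The reason for omitting age is valid for the delay regressions and does not extend to the 11 index regressions, where three quarters of the key variable has no described age adjustment and nothing else in the plan brings in age at survey.

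Whether this produces bias cannot be settled from the document. Under the assumed correlations the spurious coefficient stays below one standard error. At the lower end it is negligible. At the upper end it would be 40% of the prior mean and would nearly double the nominal 5% error rate for that outcome, which matters because Section VII expects the index to correlate only weakly with the outcomes. If ages are tightly clustered, the effect could be smaller than any value shown.

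The case for acting rests on low cost and low risk: age at survey cannot be a consequence of self-control, so adjusting for it cannot remove part of a genuine effect by conditioning on a mediator.

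**What to change.** - In Section III, add age at survey as a covariate in the 11 competence-index primary regressions and report the gender-only model beside it. At minimum, pre-specify the age-adjusted index model as a robustness check in Section V.
- Reword the parenthesis in Section III so that it applies to the delay regressions only.
- Define age at survey in Section VIII, and report its range and standard deviation so that readers can judge how much the adjustment could matter.
- If age enters the index models, add it to the imputation model in Section X.E, in keeping with the plan's own principle that every analysis variable should be included there.

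Adding age to the delay regressions is optional. The cost is one residual degree of freedom per index regression, a second column of results and a few lines of SAP text. No new data collection appears to be needed, since the team has already used respondents' ages.

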#### **A. Primary outcome variables**

- Net worth n=109
- Permanent income n=112
- Net worth / permanent income n=109
- Annual amount of interest above 6% on high cost debt n=109
- Percent of later choices in money sooner vs. later tradeoffs n=112
- Measure of misuse of credit cards n=113
- Savings rate with permanent income as a control on the RHS n=106
- General measure of financial situation n=113
- Educational attainment in years n=113
- Index of forward-looking behaviors n=113
- Social status n=113

#### **B. Primary right hand side variables**

- We will test the relationship between all primary outcomes and the following two key independent variables:
  - Delay ability: Expected deviation from predicted delay time in uncensored log seconds (measured in the marshmallow task at Bing preschool)
  - Self-regulatory competence: index of behavior including measure of delay ability, but also including self-control measures in 1984, 1993, and 2003

### **IV. Secondary analyses**

#### **A. Secondary outcome variables**

- We will test each of the five components of the index of forward-looking behaviors variable as separate secondary left-hand-side variables. These include:
  - Diet, exercise, and BMI
  - Smoking and alcohol use
  - Preventative health and dental care
  - Agreement with statements about procrastination
  - Carefully consider future consequences of current financial decisions
- We will test savings rate as an outcome variable without controlling for permanent income as a secondary analysis of savings behavior
- Because of small sample size for these measures, we will test Quantitative and Verbal SAT scores as two secondary outcome variables
- We will test the education scale as described in Ayduk et al (2000) as an additional outcome variable
- We will test current emotional state and satisfaction with present relationship as an additional outcome variable. This is a secondary outcome as we consider it to be a noisy measure of emotional well-being and happiness in relationships that focuses on current emotional states and relationships rather than stable emotional and personality traits

## B. Secondary sets of right hand side variables

- We will test the following sets of secondary RHS variables in combination with all primary and secondary outcome variables:
  - Delay ability measured in preschool (deviation from predicted delay in log seconds) and an aggregate self-control index
    - $y = \alpha + \beta_1 \times \text{delay ability} + \beta_2 \times (\text{self} - \text{control index}) + \beta_3 \times \text{male}$
  - Delay ability measured in preschool (deviation from predicted delay in log seconds) and separate self-control indices in each year (1984, 1993, and 2003)
    - $y = \alpha + \beta_1 \times \text{delay ability} + \beta_2 \times (\text{self} - \text{control index in 1984}) + \beta_3 \times (\text{self} - \text{control index in 1993}) + \beta_4 \times (\text{self} - \text{control index in 2003}) + \beta_5 \times \text{male}$
  - Delay ability measured in preschool (deviation from predicted delay in log seconds) and each of the six subscales of the self-control index (averaged across years)
    - $y = \alpha + \beta_1 \times \text{delay ability} + \beta_2 \times \text{attention subscale} + \beta_3 \times \text{coping subscale} + \beta_4 \times \text{goal pursuit subscale} + \beta_5 \times \text{concern for others subscale} + \beta_6 \times \text{delay subscale} + \beta_7 \times \text{general cognitive ability subscale} + \beta_8 \times \text{male}$

## C. Secondary tests

- Our primary analyses will be run on the full sample. Secondarily, we will run the primary analyses with the key independent variable of expected deviation from predicted delay time in uncensored log seconds for the diagnostic condition (rewards exposed/spontaneous ideation) separately from the non-diagnostic conditions (pooling conditions with suggested ideation and/or rewards covered). We hypothesize that we will see larger effects in the diagnostic condition than in the remaining conditions and will test this in two ways:
  - After orienting the coefficients such that higher values correspond to higher self-control, we will test this hypothesis by running an F-test to test whether the sum of coefficients in the diagnostic condition is significantly different from the sum of coefficients in the non-diagnostic conditions
  - We will also test the differential predictive power of delay time in the diagnostic condition by testing the following model on the full sample where  $y$  represents each of the primary outcome variables and *diagnostic* is a binary indicator for being in the diagnostic condition.  $\beta_3$  will be the coefficient of interest in these secondary tests
    - $y = \alpha + \beta_1 \times \text{delay ability} + \beta_2 \times \text{diagnostic} + \beta_3 \times \text{delay ability} \times \text{diagnostic} + \beta_4 \times \text{male}$

## V. Robustness checks

- We will replicate the primary analyses using deviation from predicted delay time in uncensored seconds (rather than log seconds) to test the sensitivity of our model to the assumption of log-normality in analysis of delay time in the marshmallow task
- We will replicate the primary analyses winsorizing the key delay ability or self-regulatory competence variable at the 5th and 95th percentile
- We will replicate the primary analyses with the key independent variable of expected deviation from predicted delay time in uncensored log seconds. In these secondary tests,

- instead of estimating a model with a linear effect of deviation in delay time, we will introduce a spline with knots at the 33.3rd and 66.6th percentiles of deviation in delay time
- We will test robustness of all analyses with self-control scores in the 1984, 1993, and 2003 surveys to the imputation method used to populate missing values. Robustness checks will include:
    - Averaging of available data years (with no imputation). In the self-regulatory competence variable, we will give the available self-control indices  $\frac{3}{4}$  weight and delay ability  $\frac{1}{4}$  weight. In secondary analyses of the self-control subscales, we will average across available years
    - A multiple imputation approach for analyses with the self-regulatory competence variable (see [Section X](#) for detailed methodology)
  - In past analyses, delay time in the marshmallow task has been measured as the deviation in seconds from the condition mean delay time. As a robustness check, we will re-test the primary analysis using deviation in seconds from the condition mean delay time instead of expected deviation from predicted delay time in uncensored log seconds derived from the Tobit random effects model
  - We will test robustness of our primary findings to assumptions made during data cleaning by dropping respondents for whom we made assumptions and repeating relevant analyses

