## **B. Expected deviation from predicted delay time (uncensored log seconds and seconds)**

- We believe raw delay times differ meaningfully across treatment conditions, by age, and by gender and therefore calculate each subject's expected deviation from the delay time predicted by a Tobit random effects model conditional on their age, gender, treatment condition, and accounting for the censoring of delay times at 900 seconds
- See [Section X](#) for detailed methodology

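### The condition-mean robustness check drops age adjustment without saying so, because the SAP's reason for omitting age holds only for the Tobit-based deviation

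*SAP*

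**What the plan says.** SAP Section III (Primary analyses) regresses each outcome on one self-regulation measure and a male dummy; permanent income is added for savings rate only. It explains the absence of age by a property of the delay predictor: "deviation from expected delay time—already takes age into account".

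That reason is accurate for the primary delay variable. Section VIII.B defines it as a deviation from the delay time "predicted by a Tobit random effects model conditional on their age, gender, treatment condition", and Section X.A.4 shows age in months as a term in that model.

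Section V (Robustness checks) then brings in a different predictor. It notes: "In past analyses, delay time in the marshmallow task has been measured as the deviation in seconds from the condition mean delay time". It plans to re-test the primary analysis "using deviation in seconds from the condition mean delay time instead of expected deviation" from the Tobit model. No covariate is added for this check.

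On whether age matters for delay, Section VIII.B says: "We believe raw delay times differ meaningfully across treatment conditions, by age, and by gender". Section X.A.2 repeats the view and gives it as a reason to standardise performance on all three factors.

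**The concern.** The SAP names three things to standardise for: condition, age and gender. In the condition-mean check, subtracting the mean handles condition and the male dummy handles gender. Nothing handles age. The one reason given for leaving age out is a property of the Tobit deviation that the substitute measure does not have.

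What is at stake is how the check is read. If age at the task is related both to waiting time within condition and to a mid-life outcome, the coefficient in this check carries an age component that the primary coefficient does not. A reader who sees the two differ would have one more explanation to weigh, and the SAP does not say that it is there.

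**Working it through.** The SAP states no figure on this point, so there is none to reproduce. The check compares the definitions and then gives an illustration of scale.

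**Step 1. What each delay predictor adjusts for**

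| Analysis | Predictor | Condition | Gender | Age |
|---|---|---|---|---|
| Primary (III, VIII.B, X.A) | Tobit deviation, log seconds | in model | in model and male dummy | in model |
| Uncensored-seconds check (V) | Tobit deviation, seconds | in model | in model and male dummy | in model |
| Winsorized and spline checks (V) | Tobit deviation, log seconds | in model | in model and male dummy | in model |
| Condition-mean check (V) | Seconds minus condition mean | subtracted | male dummy | none |

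The gap is confined to the last row.

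**Step 2. Is age available?** Section VIII.E defines age in months at the first delay experiment. Section X.A.3 describes the 113 respondents as a subset of the 543 subjects with delay time, age and gender recorded. Adding age loses nobody.

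**Step 3. Scale of a possible age component.** Take standardised variables and set the male dummy aside. Let a be the correlation of age with the condition-mean deviation, b the effect of age on the outcome, d the age-free part of delay, and t the effect of d:

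- x = a·age + √(1 − a²)·d
- y = b·age + t·d + error
- r(x, y) = a·b + t·√(1 − a²)

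The term a·b is the age-induced part. The SAP gives neither a nor b; Section IX says only that correlations of raw delay time with age were examined. I assume a from 0.1 to 0.4 and b from 0 to 0.2. With t = 0:

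| a | b = 0 | b = 0.1 | b = 0.2 |
|---|---|---|---|
| 0.1 | 0.00 | 0.01 | 0.02 |
| 0.2 | 0.00 | 0.02 | 0.04 |
| 0.3 | 0.00 | 0.03 | 0.06 |
| 0.4 | 0.00 | 0.04 | 0.08 |

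With t = 0.05, the prior mean for delay ability in Section VI.C, r runs from 0.05 × √(1 − 0.16) = 0.046 (a = 0.4, b = 0) to 0.08 + 0.046 = 0.126 (a = 0.4, b = 0.2).

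**Step 4. Benchmarks.** The standard error of a correlation at n = 113 is about 1/√(113 − 3) = 0.095. The largest value in the table is 0.08/0.095 = 0.84 of a standard error. Two of the twelve cells exceed the prior mean of 0.05: 0.06 and 0.08, at b = 0.2 with a of 0.3 and 0.4. Every cell with b = 0 is exactly zero.

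**Step 5. Effect of adding age.** Conditioning on age leaves √(1 − a²)·d in x and t·d + error in y, so the a·b term disappears.

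**The case against.** The strongest case for the SAP is that this check is a comparison with the measure used in earlier work. On that reading the absence of age adjustment is part of what separates the old measure from the new one. This has force, and it is why the measure itself should not be altered. But Section V says only how delay time was measured in the past. It does not say that the earlier regressions omitted age, or that age is left out here on purpose.

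Several stronger readings are tempting, and the SAP does not support them:

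- **That Section III is contradicted.** Its reason is tied to the Tobit deviation and is correct for it. It is never claimed for the condition-mean measure.
- **That the check fails to isolate the log and censoring model, as it was meant to.** Section V states no such aim. The log assumption has its own check, on uncensored seconds, which keeps the age adjustment.
- **That adding age would make a disagreement attributable to one cause.** The log scale, the handling of the 900-second limit and the shrinkage of condition effects would all still differ from the primary analysis.
- **That age is an established confounder.** The SAP asserts an age link for raw delay time. It reports neither the size of that link within condition nor any link between preschool age in months and a mid-life outcome. If the second link is zero, so is the bias.

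**Conclusion.** The point holds in a limited form. The stated reason for omitting age does not carry over to the condition-mean check, and the SAP neither adds age there nor says that the omission is intended. Age is a potential confounder in that one check and one of several possible sources of a difference from the primary result.

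Its size cannot be determined from the SAP. The range of about 0 to 0.08 rests wholly on assumed correlations. It stays below one standard error, although its upper part exceeds the 0.05 prior mean for delay ability. The primary delay regressions use the age-adjusted deviation, and the false discovery rate, Bayesian and Wald procedures in Section VI.A are specified for the primary tests, so none of them is touched. This is a minor improvement.

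**What to change.** In Section V, specify that the condition-mean regressions are run with age in months at the task as an added covariate, with the version without age shown beside them for comparison with past analyses. Leave the condition-mean measure as it is. One sentence should say that the remaining differences from the primary analysis are the log scale, the treatment of censoring and the shrinkage of condition effects.

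The cost is one degree of freedom in each of 11 regressions (11 primary outcomes × the one delay predictor), with no new data and no respondents lost.
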